**Methods/design:**

The GrOup-based physical Activity for oLder adults (GOAL) trial is a three-arm randomized control trial that will examine the efficacy of two different group-based exercise programs for older adults (informed by the tenets of self-categorization theory) in relation to a standard group-based exercise program. Within this manuscript we outline the design and proposed evaluation of the GOAL trial. The first arm is comprised of exercise groups made up of participants of a similar-age and of the same gender; the second arm consists of groups with similar-aged mixed gender participants; the control arm is comprised of mixed-aged mixed gender participants. We aim to compare the adherence rates of participants across conditions, as well as potential moderation effects and mediating mechanisms.

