### Aims and hypotheses

Drawing from the tenets of self-categorization theory and previous observational research our primary research question was concerned with whether older adults sustain their involvement in physical activity programs (over three and six months) when they participate in groups that are comprised of members of a similar age and same gender, relative to those taking part in similar-age but mixed-gender classes. Both of these conditions will be compared to the adherence of older adults within standard (mixed -age mixed-gender) ‘control’ physical activity groups. Second, we were interested in whether, at the end of a 3-month physical activity program, older adults in SASG (similar-age same-gender) classes will re-enroll in SASG classes over the following 3-month period (6 months in total) to a greater extent when compared to older adults in the SAMG (similar-age mixed-gender) and MAMG (mixed-age mixed-gender) conditions. Our third research question was concerned with whether any group differences among these adherence outcomes can be explained through a mediation model (with cohesion and affective attitudes as target mediators). Our fourth research question was concerned with whether there are gender differences across the primary outcome (physical activity adherence behavior) by assigned condition. Consistent with our previous findings that women demonstrate a slightly stronger preference for same-gender contexts [19] we expected that (in addition to main effects for the SASG context when compared to the mixed-gender settings), the effects for SASG versus the other two conditions (in relation to adherence) would be more pronounced for women. The following hypotheses will be tested:*Hypothesis 1.* Older adults in the SASG groups condition will demonstrate improved adherence (i.e., attendance rates) over 3-months and 6-months than older adults in the SAMG condition, who in turn will demonstrate improved adherence to those older adults in a standard (control) group-based exercise condition (MAMG).*Hypothesis 2.* A greater proportion of older adults in the SASG condition will re-enroll in the program (after 3 months for an additional 3 months; 6 months total) than those in the SAMG and MAMG groups.*Hypothesis 3.* The covariance of the assigned conditions (SASG, SAMG, MAMG) on adherence (at 3 and 6 months) will be explained (mediated) by changes in older adults’ perceptions of group cohesion and affective attitudes (enjoyment).*Hypothesis 4.* Gender will moderate the effects of the intervention conditions in relation to adherence and re-enrollment.

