#### Sample size

We powered our study to detect significant differences in individuals’ physical activity adherence (over 3 and 6 months) in the SASG groups when compared to the SAMG and MAMG standard care control condition. In order to detect a medium effect size *f* = .25 (difference between the SASG and both SAMG and MAMG conditions) based on a 2 (Gender) x 3 (Conditions) ANCOVA with the percentage of classes attended over three and six months specified as dependent variable (while controlling for baseline levels of physical activity) with power (1 - β) set at .80, and alpha set at .05, 211 participants were required across the 3 centers [59]. In order to conduct a logistic regression analysis based on individuals’ re-enrollment across the three group-based programs, based on power at .80, alpha at .05, an anticipated medium effect size (odds ratio = 2.5), and a balanced design, 167 participants were required [59].

To test for mediation through use of a cross-lagged panel model based on a structural equation modeling (SEM) approach, while modeling gender invariance, we drew from three broad criteria. First, based on recommendations provided by MacCallum et al. [60], and using Preacher and Coffman’s [61] R-code for assessing RMSEA (< .05), based on power set at .80, a minimum sample size of 163 was identified as being necessary for conducting the cross-lagged panel model (without considering gender differences). This calculation approximates with recommendations provided by Garver and Mentzer [62] that a ‘critical sample size’ of 200 is required as a general rule of thumb for providing sufficient statistical power for SEM analysis. In addition to these two sets of considerations, in light of the fact that the panel model will include a *multi-group* (males, females) component in order to examine gender invariance, this requires twice the sample size (i.e., *n* = 326, cf. MacCallum et al.; *n* = 400, [60]). Thus, in order to account for an attrition rate as high as 25 % (over the course of the program) a sample size of 540 would be sufficient to examine the mediational model proposed in this trial. In sum, we determined that an overall sample size of 540 older adults across the three arms of the trial would be sufficient for examining each of the study hypotheses.

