#### Proposed outcome analyses

Preliminary analyses will be conducted to examine whether any patterns of missing data exist (e.g., missing at random, missing completely at random, etc.) for each of the psychosocial variables (cohesion, affective attitudes) using the Missing Value Analysis (MVA; examination of Little’s chi square test) on SPSS Version 20. The data will also be examined for multivariate and univariate outliers, as well as for violations of normality, with the appropriate transformation procedures utilized. Prior to the main analyses, we will also examine invariance in the primary outcome variable (adherence over 3 and 6 months) across the two cohorts (cohort 1 – March to August 2014; cohort 2 – March to August 2015). In light of the fact the two cohorts will be examined at exactly the same time of year, using exactly the same experimental procedures, we would expect invariance in patterns of adherence across the three conditions in each year, thus supporting the pooling of data from both cohorts. Two 2 (gender) x 3 (conditions) ANCOVAs with baseline measures of physical activity (LTEQ scores) entered as a covariate, and adherence to the program over 3-months and 6-months as the dependent variable.

A logistic regression analysis will be conducted to examine the likelihood of older adults randomized to the SASG condition re-enrolling in the same SASG condition after the initial 3-month program, when compared to the re-enrollment of older adults in the SAMG and MAMG conditions. In the logistic regression model, gender will be added as an independent variable, with the regression model explained by $$ \pi =\frac{1}{1-{e}^{-x}} $$ where x = *b0* + *b1G1* + *b2 G2* + *b3 gender* + *b4G1*gender + b5G2*gender* (where *b0* is the intercept and *b1*-*b5* are the slopes for predictors). For hypotheses 1, 2, and 4, SPSS Version 20 will be used to analyze the data.

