## Discussion

Understanding the predictors of physical activity adherence is an important research endeavor within the fields of preventive medicine and health psychology. A growing body of epidemiologic evidence now exists in support of the ongoing involvement in active lifestyles among older adults, and indeed the benefits of regular activity among this population have been well-established [71]. Our proposed study will examine whether a theory-driven, evidence-based intervention has the capacity to support the sustained involvement in physical activity among older adults. The proposed research will also provide the most rigorous test to date of the efficacy of SASG physical activity settings for sustaining the physical activity behaviors of older adults. Although our previous research on exercise preferences [16, 19] as well as the predictive utility of intra-group similarity [16, 18, 20] points to the importance and viability of SASG group contexts for sustaining physical activity adherence behaviors, it should also be noted that these studies utilized non-experimental observational designs. Thus, the causal link between intra-group similarity and exercise adherence has yet to be examined.

In the current study, an experimental (RCT) design is used to examine the efficacy of SASG (and SAMG) settings, the findings of which have the potential to inform the delivery of effective health-enhancing physical activity interventions that are likely to sustain the adherence behaviors of older adults in those programs. If either the SASG or SAMG conditions have significantly higher adherence rates, when compared to the MAMG group, we will have preliminary evidence to support a *small change with substantive impact*. From a knowledge translation perspective, attending to group composition considerations is an easy, sustainable, and low-cost way to influence physical activity behaviors for older adults. This program would easily translate to a variety of physical activity settings including YMCAs, other community-centers, retirement communities, among others. The data collected in this trial have the potential to inform next steps for large-scale implementation and understanding potential mechanisms related to the efficacy of group-based interventions.

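### Hypothesis 1 claims an ordering of three arms (SASG > SAMG > MAMG), but neither the stated adherence analysis nor the sample size addresses that ordering

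*Protocol article*

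**What the plan says.** **Aims and hypotheses.** The primary question sets SASG "relative to those taking part in similar-age but mixed-gender classes", and the next sentence compares both similar-age conditions with the control classes. Hypothesis 1 is a directional chain over 3 and 6 months: SASG does better than SAMG, "who in turn will demonstrate improved adherence to those older adults in a standard (control) group-based exercise condition (MAMG").

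**Proposed outcome analyses.** Adherence is analysed by "Two 2 (gender) x 3 (conditions) ANCOVAs with baseline measures of physical activity (LTEQ scores) entered as a covariate", one model for 3 months and one for 6 months. No arm contrast or direction is attached.

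**Sample size.** The trial is powered for adherence "in the SASG groups when compared to the SAMG and MAMG standard care control condition". The "medium effect size *f* = .25" is glossed as the "difference between the SASG and both SAMG and MAMG conditions". With power .80 and alpha .05 the section arrives at 211. It then sets the overall total at 540, mainly for the mediation model with attrition of up to 25%, and closes by saying that 540 is enough for every hypothesis.

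**Discussion.** A favourable implication is drawn "If either the SASG or SAMG conditions have significantly higher adherence rates, when compared to the MAMG group". SASG versus SAMG plays no part in that sentence.

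**The concern.** Hypothesis 1 has two links, SASG > SAMG and SAMG > MAMG. The sizing text omits the second and the Discussion sentence does not depend on the first. The condition effect of the stated ANCOVA tests neither, because it rejects for any inequality among the three arm means, including one with SAMG or MAMG on top.

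The two links answer different questions. SASG versus SAMG isolates gender matching on top of age matching. SAMG versus MAMG isolates the similar-age package, which the protocol says includes older volunteer instructors, T-shirts and social time. A significant condition effect cannot say which of these worked. The sizing section's general assurance about 540 also leaves the impression that the ordered claim is well powered.

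**Working it through.** **1. Inputs.** From the Sample size section: f = .25, power .80, alpha .05, stated N = 211, total 540, attrition up to 25% (540 × 0.75 = 405). Assumed, because the article does not give them: 1:1:1 allocation (180 per arm, or 135 after attrition), independent observations, no variance reduction from the covariate, f = .25 read as the spread of the three arm means, and two-sided .05 for each contrast.

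**2. Reproducing 211.** Noncentral F with noncentrality N·f² and denominator df = N − 6 − 1, searching for the smallest N with power .80:

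| Numerator df | What it tests | N |
|---|---|---|
| 1 | a single contrast | 128 |
| 2 | condition effect, or gender-by-condition interaction | 158 |
| 3 | – | 179 |
| 4 | – | 196 |
| 5 | all six cells | **211** |

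Only the 5-df test returns 211. That figure does not size the condition effect or any arm contrast. It is not too small for the condition effect, whose power is 91% at 211, 99.7% at 405 and 99.97% at 540.

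**3. The condition effect does not see order.** At N = 405 and f = .25 it has about 99.7% power whatever the pattern of means. That includes SAMG above two equal arms, which contradicts the first link of Hypothesis 1.

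**4. Power for Hypothesis 1 as worded.** Take equal steps, with arm means (d, 0, −d) and SD 1. Then f² = 2d²/3, so d = .25 × √1.5 = 0.306.

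Per link, power ≈ Φ(d/√(2/n) − 1.96):
- n = 180: 0.306/0.1054 = 2.905, and Φ(0.945) ≈ 83%.
- n = 135: 0.306/0.1217 = 2.516, and Φ(0.556) ≈ 71%.

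The two contrasts share the SAMG mean with opposite signs, so their correlation is −0.5. The bivariate normal probability that both succeed is:
- N = 540: about 66%.
- N = 405: about 45%.

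Simulation with 200,000 runs gave 65.8% and 44.9%. For scale, 80% joint power needs about 224 per arm: 672 analysed, or 672/0.75 = 896 enrolled.

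**5. Discussion sentence against Hypothesis 1.** Take 135 per arm and observed means of +0.177, +0.177 and −0.354 SD.
- Condition effect: F = 135 × (0.177² + 0.177² + 0.354²)/2 = 12.7, p < .0001.
- SAMG − MAMG and SASG − MAMG: t = 0.531/√(2/135) = 4.36, p < .0001.
- SASG − SAMG: t = 0, p = 1.0.

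The Discussion's condition is met, while the first link of Hypothesis 1 has no support.

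**The case against.** This is a condensed journal article and the analysis plan is not shown. Planned contrasts may be written there, and the article nowhere says that a significant condition effect decides Hypothesis 1. That stands: missing follow-up tests alone would be no finding. What remains is on the page. The sizing omits one link of the hypothesis, 211 matches neither the condition effect nor a contrast, and 540 is declared sufficient for every hypothesis.

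A reader might infer that the protocol names four rival deciding comparisons, so that the same data could support opposite conclusions. The text does not support that. Read with its second sentence, the primary question covers all three arms and agrees with Hypothesis 1. The sizing text describes an effect and the Discussion sentence an implication; neither is a decision rule. If the full chain holds, every one of these statements is satisfied. They part only when a link fails, and then they differ in what counts as success, not in the direction of an effect.

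A reader might also take the sizing to mean SASG above two equal arms, and point out that at N = 540 the condition effect would then be significant with Hypothesis 1 not shown in about 97.5% of trials. The protocol does not say that SAMG and MAMG are equal. Under that pattern the second link is false, and failing to confirm it is correct behaviour.

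**Conclusion.** The mismatch is real and moderate. Hypothesis 1 is an ordered claim, the stated model's condition effect cannot confirm an order, and the sizing addresses a different set of comparisons. The condition effect itself is amply powered. Power for the ordering is about 66% with all 540 analysed and 45% at 405, so the general sufficiency claim does not hold for Hypothesis 1 at the conventional 80%.

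The joint figures rest on the assumptions in step 1 and on equal steps. For the same f, unequal steps would make one link easier and the other harder. A useful covariate would raise power, and correlation within classes would lower it. The point does not show that the trial would reach a wrong conclusion, or that the investigators intend to choose a contrast after seeing the means. The Trial status section says that no data had been analysed.

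**What to change.** In Proposed outcome analyses, test Hypothesis 1 with two planned contrasts from the same ANCOVA, SASG minus SAMG and SAMG minus MAMG, each at two-sided .05 at each time point. Call the ordering supported at a time point only if both are significant in the stated direction. Because both must succeed, alpha need not be split between them. Report SASG minus MAMG and the condition effect as supportive. Neither link should also be singled out as the sole primary contrast, since that would set a second criterion for the same hypothesis.

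In Sample size, say which test 211 refers to, add SAMG versus MAMG, and replace the general sufficiency claim with the power for each link and for both, with the assumptions stated. In the Discussion, separate the implication of a similar-age arm beating MAMG from support for Hypothesis 1.

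The change is one of wording and uses the same model and data. Both cohorts are already randomized and no further enrolment is asked for. The price is a less favourable stated power for Hypothesis 1.

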## Method

### Study design

The GrOup-based physical Activity for oLder adults (GOAL) Trial is a 3-arm randomized controlled trial (RCT) developed in alignment with the tenets of self-categorization theory. The study has been approved by the Behavioral Research Ethics Board at The University of British Columbia, and is registered with ClinicalTrials.gov (# NCT02023632).

The design, conduct, and reporting of this study will adhere to the Consolidated Standards of Reporting Trials (CONSORT) guidelines [36]. The pre-screening process included the completion of the Physical Activity Readiness Questionnaire for Everyone (PARQ+) and Electronic Physical Activity Readiness Medical Examination (ePARmed-X+) [37]. Pre-screening was conducted either by a trained research assistant or the project coordinator (authors [name] and [name]) using a pre-screening script for consistency. If the ePAR-medX+ highlighted that the interested older adult needed physician approval prior to joining the program, the research assistant informed the individual and indicated that subsequent physician approval was required before s/he then could enroll in the study. Following the initial screening process for inclusion/exclusion, informed consent was obtained, and participants were randomized to one of three study arms:Similar-Age Same-Gender (SASG)Similar-Age Mixed-Gender (SAMG)Mixed-Age Mixed-Gender (MAMG)

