### Participants

We aimed to recruit 540 older adults that would be randomized across the three conditions. To be eligible participants needed to be 65 years of age or older (targeted recruitment of 50 % female and 50 % male) and not have contraindication which might prevent them from participating in moderate-intensity physical activity. To both effectively manage the trial and avoid unnecessary burden on the respective YMCA centers, the trial was designed to run in two (*N* = 270 in cohort 1, and *N* = 270 in cohort 2) cohorts. The first cohort ran between March and August 2014 and the second cohort is running between March and August 2015. Both cohorts are run within the same March-August window in order to minimize any seasonal effects between cohorts.

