### Study interventions

The trial is taking place at three different YMCA centers in the Lower Mainland of British Columbia, over 2 years. The group exercise classes take place in 3-month blocks with the opportunity to re-enroll in the same program for another 3 months, thus lasting 6-months in total (see Fig. 1). Each program is run on the basis of classes taking place three days per week, with classes lasting 50–60 min. This dosage (150–180 min/week) is consistent with Canada’s current physical activity guidelines for older adults engaging in ≥ 150 min of moderate-to-vigorous physical activity per week [38], as well as findings from the Canadian Community Health Survey [39] which found that 67 % of seniors who are active three or more times a week are in good health, compared to 36 % who are infrequently active.

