**Fig. 1 Fig1:**
[figure not shown]
Flow of participants through the trial

The design of the SASG physical activity condition was informed by the tenets of self-categorization theory as well as the results of a recent case study of a highly efficacious physical activity program entitled the *Lively Lads* (a pseudonym) for older adult males [22]. Although the *Lively Lads* program was developed by-seniors-for*-*seniors, it made use of a number of salient theory-driven group dynamics strategies that appear to be implicated in its success. Several of the *Lively Lads* strategies were utilized in the design of the SASG intervention arm of the GOAL Trial. First, one of the core features of this condition is that it designed exclusively for those of a similar age and same gender. Such an environment was reported by Dunlop and Beauchamp [22] to provide opportunities for social connectedness, as well as personal comfort (e.g., reduced likelihood of embarrassment and displays of physical incompetence in front of women). Second, the volunteer exercise class instructors are drawn from the ranks of older adults. Such an approach is consistent with research from the perspective of social cognitive theory, highlighting the value of ‘similar models’ as sources of vicarious efficacy enhancement information and verbal persuasion [40]. From the perspective of program sustainability, volunteer exercise leaders enable the program to keep its costs low (there are no costs involved in paying instructors, as they are volunteers). Consistent with social identity and self-categorization perspectives, the program also makes use of a series of strategies to foster group identity (e.g., providing participants with T-shirts to foster a sense of ‘distinctiveness’). Finally, although a major objective of the SASG intervention condition is to engage in physical activity, an important strategy (informed by both social identity theory and the *Lively Lads* program) is to provide opportunities for the older adults to connect with one another after the classes have ended (e.g., post-workout coffee gatherings). Although the *Lively Lads* program was developed with older adult males, classes are also provided in the GOAL Trial for older adult women at each YMCA site.

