Mediation will be tested through use of a multi-group (to examine whether the effects are invariant across gender) cross-lagged panel model using a structural equation modeling (SEM) framework. Cross-lagged panel models are a type of auto-regressive modeling. This approach was proposed by Cole and Maxwell [64] for longitudinal data and will be adapted for the purpose of the present study. This approach has two advantages. Specifically, it allows us to examine the reciprocal relations between the mediators (cohesion and affective attitudes), and the outcome (adherence). In a recent paper we indicated the importance of assessing group cohesion throughout the lifespan of a physical activity group, and not just through a single time-point early-program measure (this has been the most commonly used method of assessing cohesion as a mediator within group dynamics physical activity research [65]). This panel modeling approach, in which all the variables are measured at multiple time points, can rigorously test the prospective relations between predictors (assignment to experimental condition), mediators, and outcomes (i.e., predictors prior to mediators and mediators prior to outcomes). The cross-lagged panel model will be estimated using Mplus 7.2 with a full information maximum likelihood (FIML) estimator used to handle missing data [66]. This procedure will use all available data points for parameter estimation under the assumption that the data are missing at random. FIML estimation tends to produce less biased estimates than deletion or simple missing data imputation techniques (e.g., EM algorithm, regression, listwise/pairwise deletion, mean replacement) even when data are not missing at random [67]. By examining multi-group models, this will allow us to examine whether the structural pathways are invariant across genders.

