There are a few potential limitations to address at the onset. First, the MAMG is unique in that participants can choose any 3-day per week class offered at the YMCA. From a design perspective, there may be a limitation in giving MAMG participants choice in terms of which YMCA course they wished to participate, since participants in the SASG and SAMG conditions were not given any such choice. However, from a pragmatic perspective, we believe that the MAMG group represents the most appropriate type of control condition as it reflects the typical type of exercise class available within community exercise settings. Thus, MAMG provides a strong point of comparison.

There may also be critique of variation related to class leaders. Measures were taken in the extensive training of the volunteer, similar-aged instructors. All volunteer leaders were trained at the same time, through the three modules outlined above. In this way, we sought to increase the likelihood of treatment fidelity across all conditions at each site. However, there may be some inherent differences based on instructor personalities, level of exercise instructor experience, and so forth. To account for these potential differences across conditions and sites, the process evaluation includes queries about perceptions of the class leaders (e.g., leadership and communication style).

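### The stated models treat classmates as independent: if attendance is correlated within classes, type I error exceeds 5%, and the required sample sizes make no allowance for it

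*Protocol article*

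**What the plan says.** The unit of randomisation is the person: after screening and consent, "participants were randomized to one of three study arms" (Study design). Treatment is delivered in groups. Under Study interventions, SASG and SAMG classes have volunteer older-adult instructors, T-shirts to build group identity and social gatherings after class. SASG classes are single-gender: the model programme was for men, and "classes are also provided in the GOAL Trial for older adult women at each YMCA site". MAMG participants instead pick a regular YMCA class.

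Under Mediators, group cohesion is one of the two proposed routes from condition to adherence.

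Proposed outcome analyses fixes three models:
- **Adherence at 3 and 6 months:** "Two 2 (gender) x 3 (conditions) ANCOVAs with baseline measures of physical activity (LTEQ scores) entered as a covariate".
- **Re-enrolment:** a logistic model written out term by term, with an intercept, two condition terms, gender and two condition-by-gender products.
- **Mediation:** a two-group cross-lagged panel model "estimated using Mplus 7.2 with a full information maximum likelihood (FIML) estimator used to handle missing data", with no cluster or multilevel option mentioned.

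Sample size states that "211 participants were required across the 3 centers" for the ANCOVA, 167 for the logistic model and 326 or 400 for the mediation model, and settles on 540. No ICC or design effect appears.

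The Discussion grants that instructors may differ in personality and experience. It points to their common training and then says: "To account for these potential differences across conditions and sites, the process evaluation includes queries about perceptions of the class leaders".

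**The concern.** People who attend the same class share a timetable, a room, fellow members and, in all likelihood, an instructor. The theory under test says that members affect one another's attachment to the group. Attendance within a class should therefore be positively correlated, and an ICC of exactly zero would sit badly with the trial's own rationale. A model with only person-level error counts each classmate as a fully independent observation, so its standard errors are too small.

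This matters most for Hypothesis 1, where a few well-run or well-timed classes can look like a condition effect. It also reaches Hypothesis 4. Every SASG class holds one gender, so in that arm men and women are compared between classes, yet the test uses person-level error. Interview questions about class leaders can help to interpret a result but cannot correct a standard error.

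The same independence assumption underlies the sample-size figures.

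**Working it through.** **Inputs from the article.** "We aimed to recruit 540 older adults that would be randomized across the three conditions", so 180 per arm if equal. "The trial is taking place at three different YMCA centers in the Lower Mainland of British Columbia, over 2 years", so 3 × 2 = 6 site-years. Equal recruitment of men and women is intended. Attrition of up to 25% leaves 540 × 0.75 = 405.

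**Assumptions, because the article gives no figure.** One SASG class per gender and site-year gives 12 classes of 15. SAMG has 6 classes of 30 or 12 of 15. MAMG ranges from fully independent to clustered like SAMG. ICC runs from 0 to 0.10.

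**Step 1: reproduce the stated numbers under independence.**
- ANCOVA: noncentral F with λ = N f², f = 0.25, α = 0.05, power 0.80 and 5 numerator degrees of freedom gives N = 211 exactly.
- Logistic: the two-sided Wald formula for OR 2.5 with 1:1 allocation and an assumed reference rate of 0.50 (comparator 0.714) is 2 × (1.96 + 0.842)² × (1/0.25 + 1/0.204) / (ln 2.5)² ≈ 166.4, so 167.
- Mediation: 400 / 0.75 = 533.3, so 534, which 540 covers.

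All three follow with a design effect of 1.

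**Step 2: apply a design effect, DE = 1 + (m − 1) × ICC.**

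| m | ICC | DE | 211 becomes | 167 becomes | 400 becomes |
|---|---|---|---|---|---|
| 15 | 0.01 | 1.14 | 241 | 191 | 456 |
| 15 | 0.02 | 1.28 | 271 | 214 | 512 |
| 15 | 0.05 | 1.70 | 359 | 284 | 680 |
| 15 | 0.10 | 2.40 | 507 | 401 | 960 |
| 30 | 0.05 | 2.45 | 517 | 410 | 980 |

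For the mediation model this multiplier is only a rough guide.

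**Step 3: set these against 405.** The largest design effect that 405 can absorb is:
- ANCOVA: 405/211 = 1.92 (ICC about 0.066 at m = 15, 0.032 at m = 30).
- Logistic: 405/167 = 2.43 (ICC about 0.10 and 0.049).
- Mediation: 405/400 = 1.01, or 405/326 = 1.24 if the smaller target is used.

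**Step 4: type I error of the planned ANCOVA.** The 2 × 3 model was simulated under the null with a class random effect (N = 540, 10,000 runs per setting). Omnibus condition test, nominal 5%:

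| SAMG layout | MAMG | ICC 0 | 0.01 | 0.02 | 0.05 | 0.10 |
|---|---|---|---|---|---|---|
| 6 classes of 30 | clustered | 5.3% | 9.0% | 13.4% | 25.3% | 42.2% |
| 6 classes of 30 | independent | 5.2% | 7.1% | 10.1% | 17.8% | 27.6% |
| 12 classes of 15 | clustered | 5.2% | 6.9% | 9.3% | 17.3% | 29.8% |
| 12 classes of 15 | independent | 5.3% | 7.0% | 8.0% | 12.5% | 21.3% |

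In the clustered rows, MAMG has the same layout as SAMG.

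The gender-by-condition test gives 8.0–8.7% at ICC 0.05 and 11.8–12.9% at 0.10.

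**Step 5: closed-form checks at ICC 0.05.** For SASG against SAMG (12 classes of 15, 6 of 30), the mean design effect is (1.70 + 2.45)/2 = 2.075 and the error is 2 × [1 − Φ(1.96/√2.075)] = 17.4%. The simulation gave 17.4–17.5%. For the omnibus test in the first row, the mean design effect is (1.70 + 2.45 + 2.45)/3 = 2.20 and the error is about exp(−2.996/2.20) = 25.6%. A somewhat more concentrated control arm, with a mean design effect of 2.35, gives exp(−2.996/2.35) ≈ 28%. At ICC 0.01, the last row has a mean design effect of (1.14 + 1.14 + 1)/3 = 1.093 and an approximate error of 6.5%. Hence the summary ranges of 6–9%, 13–28% and 21–42%.

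**The case against.** The best reply concerns power. The trial plans 540, not 211, and the article presents 211 and 167 as minimum requirements. An analysis of class means under similar assumed layouts, at f = 0.25, keeps power near 95% at ICC 0.05 and 82–86% at 0.10 with 540. With 405 the figures are 90–93% and 78–83%. This stands: a reader might infer that the trial is too small for its adherence question, and the figures do not support that. Spare participants do not, however, restore the 5% error rate of a model without a class term.

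Other replies stand in part:
- A reader might take all three arms to be in fixed classes. MAMG participants choose among regular classes, so the description fits SASG and SAMG only. Treating MAMG as fully independent still gives about 13–18% at ICC 0.05.
- The size of the inflation rests on layouts and ICCs that the article does not give, and at ICC 0 the test holds its level. That clustering can inflate the error is supported; a definite figure is not.
- Instructor variation is not ignored. Volunteer leaders had common training in three modules, which may reduce class variance. It does not remove the need for a class term.
- The simulation covers the ANCOVA. The logistic model makes the same independence assumption, but the amount of inflation for re-enrolment was not computed.

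An unseen analysis plan is a weak defence here, because the article writes its models out, the logistic one in full.

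**Conclusion.** The point holds in conditional form. The stated ANCOVAs, logistic regression and mediation model carry no allowance for class. If the ICC is positive, as the cohesion theory and the Discussion's remark on instructors imply, their standard errors are too small and the nominal 5% level is exceeded. Under the assumed layouts the condition test has an error of roughly 6–9% at ICC 0.01, 13–28% at 0.05 and 21–42% at 0.10. The gender-by-condition test has about 8–9% at 0.05 and 11–13% at 0.10.

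The required numbers 211, 167 and 326/400 assume independence. The planned 540 leaves real slack for adherence and re-enrolment, up to design effects of about 1.9 and 2.4 after attrition. For the mediation model it leaves practically none if 400 is the target. The finding therefore concerns error control first, and sample size mainly for mediation. Because this touches the primary question, it should be settled before analysis.

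**What to change.** Trial status reports that no data from either cohort have been analysed, so the change can still be prespecified.

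1. **Adherence:** replace the ANCOVAs by linear mixed models with the same fixed effects plus a random intercept for class, nested in site and cohort, using Satterthwaite or Kenward-Roger degrees of freedom.
2. **MAMG:** assign members to the class attended where this is recorded, and otherwise treat them as unclustered (a partially nested model). The article describes access-card attendance reports and enrolment records, but does not say that each MAMG member's class is captured. This should be checked first.
3. **Re-enrolment:** use a mixed-effects logistic model, or GEE with a small-sample correction.
4. **Mediation:** use cluster-adjusted standard errors, and state the small number of classes as a limit.
5. **Sample size:** restate the required numbers with a design effect over ICC 0.01–0.10, giving the assumed class sizes.

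No new participants or procedures are needed if class membership is on file. The price is wider intervals, less favourable stated requirements, and variance components estimated from few classes.
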